**Fig. 1 Fig1:**
[figure not shown]
Course of events for both quantitative arms

**Fig. 2 Fig2:**
[figure not shown]
Timeline of data collection

### Quantitative data analysis

To judge the feasibility of the routine integration of EPC into clinical practice at CCCs, we will measure how many eligible patients were referred to the center’s PC physician within the first eight weeks after diagnosis. For this, we will rely on the internal records of the participating centers.

With an expected response rate of ca. 50 %, we aim for a sample size of 1000 patients (200 per participating CCC) in the preliminary study phase and an additional 1000 patients (200 per participating CCC) in the main study phase. Differences between the control group (patients in the preliminary study phase) and the intervention group (patients in the main study phase) will be analyzed with respect to symptom burden, QoL, and mood. The longitudinal data (i.e. at 12 and 24 weeks) will be analyzed in regard to changes between the baseline measurement and follow-up measurements. Effect sizes between 0.20 and 0.49 will be judged as small, between 0.50 and 0.79 as medium, and above 0.80 as large [20]. We will use descriptive data analysis along with t-tests, chi-square tests, Mann–Whitney-U tests, and multivariate linear and binary logistical regression models. All statistical tests will be two-sided, and p-value ≤ 0.05 will be considered significant. IMB SPSS (Version 21.0) will be used to conduct data analysis.

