## Background

The primary goal of palliative care (PC) is to ensure quality of life (QoL) for patients with incurable, life-limiting diseases and their caregivers. This is true for all patients, regardless of their disease (e.g. amyotrophic lateral sclerosis, multiple sclerosis, heart failure, chronic obstructive pulmonary disorder, etc.) However, patients with incurable cancer remain one of the largest patient groups with a need for palliative care [1]. Due to the continuing advances in cancer treatment, cancer is likely to increasingly become a chronic disease [2].

In the past and even today, PC has often been falsely equated with end-of-life care [3]. For this reason, treatment goals in standard oncology care have often focused solely on prolonging life rather than improving QoL early in the course of the disease [4]. Even in early stages of the disease, patients with incurable cancer often suffer from multiple physically burdensome symptoms (e.g. pain) [5] and psychosocial and spiritual anxiety. By focusing on life-prolonging treatment options, the suffering that patients and their families experience from these symptoms often goes unnoticed and is not adequately relieved [3]. The outdated dictum “first prolong life, then improve quality of life” should be replaced by a holistic, integrative model [6]. This approach is referred to as early palliative care (EPC). According to this model, specialist palliative care expertise focused on the needs of the patient should be offered alongside standard oncology care [7].

For patients with non-small cell lung cancer (NSCLC), Temel et al. [8] showed that EPC improved patients’ QoL, reduced the incidence of depression, and decreased the number of aggressive (and generally futile) therapies at the end of life. In addition, EPC increased patients’ survival time [8]. In a randomized study with patients suffering from different cancer entities, Zimmermann et al. [9] found that patients who received EPC not only had a better QoL but also a higher level of satisfaction with their treatment compared to those in the control group, who were not offered EPC.

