To evaluate the feasibility of the routine implementation of EPC in CCCs, the study is built upon a convergent parallel design [15]. The quantitative arm is conceived as a multi-center, prospective cohort study with a sequential control group design. Both in the preliminary and main study phase, patients will be surveyed at three points in time (baseline, 12 weeks, 24 weeks). Standardized questionnaires will be used to measure patients’ QoL, symptom burden and mood. The economic effects of EPC will be measured using an expense log or cost diary.

In light of the objective to test the feasibility of EPC, the qualitative arm of the study consist of four interview studies with palliative care physicians, oncologists/department heads, patients and their families/caregivers. These interviews will explore: (1) which factors encourage and hinder the early integration of palliative care into standard oncology care and (2) what support patients and their families would like from palliative care and to what extent these needs can be met through the EPC approach used in this study.

After conclusion of the study, the results of the quantitative and qualitative arms will be synthesized and evaluated with regard to the feasibility of EPC in CCCs.

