### Quantitative arm

#### Participants

The EPC services provided in this study are aimed at patients with advanced metastatic cancer that is unresponsive to curative treatments (ICD 10 C 1–80 plus ICD 10 C 78–79). In all participating CCCs, patients will be identified in the tumor boards of each center. As soon as the diagnostic process has been concluded and treatment has started (i.e. within the first eight weeks after diagnosis), patients will be referred to the PC physician. Table 1 shows the inclusion and exclusion criteria for participation.

**Table 1 Tab1:** Inclusion and exclusion criteria for participation in the quantitative study arm

Inclusion criteria:	
1.	Initial diagnosis of a metastatic, incurable cancer (ICD 10 C 1–80 plus ICD 10 C 78–79) occurred within the last eight weeks, particularly:
	- non-small cell lung cancer (NSCLC) without epidermal growth factor (EFGR) mutations: met. NSCLC Stage IV – ICD C34.[01239] + metastasis code or C34.8 (multiple subdomains) + possibly M8012/3 (large cell carcinoma)
	- met. esophageal carcinoma Stage IV – ICD C15.[123459] + metastasis code or C15.8 (multiple subdomains) + possibly M8070/3 (squamous cell carcinoma)
	- met. stomach carcinoma Stage IV - ICD C16.[01234569] + metastasis code or C16.8 (multiple subdomains) + possibly M8145/3 (adenocarcinoma, diffuse)
	- non-endocrine pancreas carcinoma Stage IV - ICD C25.[012379] + metastasis code or C25.8 (multiple subdomains) + possibly M8971/3 (pancreas blastoma)
	- center-specific tumor entities
2.	Age ≥ 18 years
3.	Ability to understand written and verbal questions in German
4.	Willingness to participate in the study
5.	Informed consent
Exclusion criteria:	
1.	Other hemato-oncological disease (e.g. leukemia)
2.	Dementia
3.	Psychosis/delirium
4.	Major depression

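### The quality-of-life comparison of two non-randomized phases lists unadjusted tests and regression as equals; a model adjusted for baseline and case mix should decide.

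*Protocol article*

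**What the plan says.** The protocol article describes the design so: "The quantitative arm is conceived as a multi-center, prospective cohort study with a sequential control group design" (The design of the study). Patients are therefore allocated by calendar period, not at random.

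Under Quantitative data analysis, "Differences between the control group (patients in the preliminary study phase) and the intervention group (patients in the main study phase) will be analyzed", on symptom burden, QoL and mood. The 12- and 24-week data "will be analyzed in regard to changes between the baseline measurement and follow-up measurements". The methods follow in one sentence: "We will use descriptive data analysis along with t-tests, chi-square tests", then Mann–Whitney tests, "and multivariate linear and binary logistical regression models". No method is tied to an outcome or given precedence. A two-sided threshold of 0.05 applies to every test.

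Three patient-completed instruments (POS, QLQ-C30, HADS) are repeated at 12 and 24 weeks (Outcome assessment). Table 1 admits lung, esophageal, stomach and pancreatic cancers and also "center-specific tumor entities". Of the cited study in non-small cell lung cancer, the Background says: "In addition, EPC increased patients’ survival time".

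**The concern.** Without randomization, the two phases may differ in tumor mix and in how ill patients are at entry. The article itself describes one route: before the main phase, cancer specialists are briefed with brochures, newsletters and tumor-board presentations, and this could change who is put forward. A t-test or Mann–Whitney test makes no allowance for such a shift and would report it as an effect of EPC. Because the list is unranked and shares one threshold, an unadjusted result counts as much as an adjusted one, and the two may disagree.

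There are three lesser issues. A change score makes less efficient use of the baseline than covariate adjustment does. Several instruments and visits are tested with none leading. A change score also exists only for patients alive and answering, and that set could differ by phase if EPC affects survival.

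At stake is the stated aim of learning about the effect on QoL. The preliminary-phase patients were recruited as the reference group for that comparison.

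**Working it through.** **1. The plan's own figure.** 5 centers × 200 = 1000 per phase, 2000 in total, as stated. No target effect, SD or power is given, so there is no power calculation to reproduce. For orientation, at a standardized difference of 0.20 (the plan's lower limit for a small effect) and two-sided 0.05, power is 99.4% with 1000 per phase. It is 88.5% with 500, which applies if the expected 50% response is taken from the 1000; the text does not settle this. Random error is not the main weakness.

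**2. Residual bias and false positives.** Let b be a bias in SD units of the analyzed variable (assumed) and n the number per phase. With no true effect, the rejection rate is 1 − Φ(1.96 − b/√(2/n)) + Φ(−1.96 − b/√(2/n)).
- n = 1000, √(2/n) = 0.0447: b = 0.05 gives 20.1%; b = 0.10 gives 60.9%.
- n = 500, √(2/n) = 0.0632: b = 0.05 gives 12.4%; b = 0.10 gives 35.3%.

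The large sample makes a bias well below 0.20 SD likely to reach significance.

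**3. Change score against baseline adjustment.** With equal variances and baseline–follow-up correlation r (not in the document), the variance is proportional to 2(1 − r) for the change score and 1 − r² with baseline adjustment. The ratio of adjusted to change-score variance is (1 + r)/2.
- r = 0.3: 0.65. r = 0.5: 0.75. r = 0.6: 0.80. r = 0.8: 0.90.
- For equal precision, the change score needs 54%, 33%, 25% and 11% more patients, respectively.

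**4. Baseline imbalance.** If the phases differ by 0.20 SD at baseline (assumed), the two estimates differ by 0.20(1 − r): 0.14 SD at r = 0.3, 0.10 at 0.5 and 0.06 at 0.7. The choice between them therefore matters and should be fixed beforehand.

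**5. Multiplicity.** Three instruments × two follow-ups = 6 comparisons. If independent, 1 − 0.95⁶ = 26.5%. These scores come from the same patients and are correlated, so the true figure is lower, though above 5%.

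**6. Survivor selection.** Let QoL correlate ρ with remaining in follow-up, and let proportions s₀ and s₁ answer. The shift in the observed difference is ρ[φ(t₁)/s₁ − φ(t₀)/s₀], where t = Φ⁻¹(1 − s). All inputs are assumed.
- 60% vs 70%: 0.497 − 0.644 = −0.147. Times ρ = 0.2 to 0.5, this gives −0.03 to −0.07 SD, against the phase with more responders.
- 60% vs 65%: 0.570 − 0.644 = −0.074, giving −0.015 to −0.037 SD.
- Equal proportions with the same selection: zero.

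A simulation with 400,000 patients per scenario assumed no QoL effect, median survival 39 weeks, log-hazard 0.5 per SD of decline and an EPC hazard ratio of 0.7. It gave (−0.158 + 0.102)/0.86 = −0.065 SD at week 24. With a log-hazard of 0.2 or a hazard ratio of 0.85, this falls to about 0.01 to 0.03 SD.

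**The case against.** The strongest reply is that multivariable regression is already in the list and can adjust for case mix and baseline. A reader who stops partway through the sentence might infer that the comparison rests on t-tests and Mann–Whitney tests. The text does not support that, and it assigns no particular test to the change scores. What stands is that nothing says regression decides.

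Second, covariate lists, handling of deaths and multiplicity rules are commonly left to a statistical analysis plan or full protocol, neither of which is shown. Their absence alone is no defect. The point here concerns what the article does state: an unranked list and one threshold for a non-randomized comparison.

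Third, center is not confounded with phase if recruitment meets the target, because each center is to contribute 200 patients to each phase. Tumor entities that differ between centers do not show a difference between phases, since the same centers and criteria serve both. This stands. A shift over time is possible but not shown, and center belongs in the model as a source of variation.

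Fourth, QoL is secondary to the 75% referral criterion, and no confirmatory QoL claim is made. This too stands and limits the weight of the point.

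**Conclusion.** The point holds as a moderate one. The plan should say that an adjusted model decides the QoL comparison, because an unadjusted test between consecutive cohorts cannot separate EPC from a change in case mix. The 20% to 61% false-positive range applies with 1000 per phase if 0.05 to 0.10 SD of bias remains. The document gives no means of knowing whether it would.

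Some stronger readings are not supported:
- **That the result is biased.** This is a risk of unknown size. Nor does adjustment guarantee an unbiased answer without randomization.
- **That baseline information is wasted.** Change scores use it, less efficiently. The loss disappears if baseline is a covariate, even with change as the outcome.
- **That survivor selection hides or reverses a benefit.** The shift is roughly 0.02 to 0.07 SD under assumed inputs. A true 0.20 SD would still appear as about 0.20 − 0.065 = 0.135 SD. The survival gain cited is for lung cancer, while this cohort is mixed.
- **That the familywise error is 26% or more.** That figure requires independence. Adding the caregiver's questionnaire on dying would go beyond the stated comparison of symptom burden, QoL and mood.

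**What to change.** - Make the regression already listed the deciding QoL analysis: a linear mixed model of the T1 and T2 scores on phase by visit, adjusted for baseline score, center and tumor entity.
- Keep t-tests, chi-square and Mann–Whitney tests for description.
- Name one leading QoL outcome and time point in advance (QLQ-C30 global QoL at 12 weeks is one candidate) and call the rest supportive.
- Report deaths and non-response by phase beside the model, with a sensitivity analysis for death, such as ranking it as the worst outcome.
- State that adjustment reduces but does not remove confounding between the phases.

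The cost is some wording and a little more programming. The model uses data the study already plans to collect, and the named software fits mixed models. The real price is that fewer results can be called confirmatory.

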### The qualitative arm

#### Participants and sampling

The qualitative arm of the EVI project consists of four interview studies (Table 2). Interview partners for each study will be recruited equally from each participating CCC.

**Table 2 Tab2:** Planned qualitative interviews at each participating CCC

	Preliminary phase:	Main phase:
	Number of interviews per center	Number of interviews per center
Palliative care physicians	1	1
Oncologists	5	5
Department heads	5	5
Patients	5	5
Family/caregivers	5	5
Total	21	21

##### Interview study with PC physicians

The five PC physicians hired for the project will be interviewed both in the preliminary and main study phase regarding the feasibility of integrating EPC into standard oncology care. In addition, the PC physicians will be asked what factors support and hinder the process of establishing EPC in their respective center.

##### Interview study with oncologists and department heads

During the preliminary and the main study phase, we will conduct expert interviews with 25 oncologists and 25 department heads. The focus of these interviews will be the feasibility of the routine integration of EPC into standard oncology care. The sample of oncologists and department heads will be achieved by using maximum variation sampling.

##### Interview study with patients and family/caregivers

During the preliminary and the main study phase, 25 patients and 25 family members/caregivers will be interviewed regarding what kind of support they would like from palliative care in addition to standard oncology care and how they perceive the provided EPC. The patient and caregiver samples will also be achieved by using maximum variation sampling. All patients and caregivers will be recruited from the quantitative arm of the study.

In total, we aim at 210 interviews for the qualitative arm of the project.

### Outcome assessment

To adequately assess the feasibility of integrating EPC into standard oncology care, it would be insufficient to only measure whether 75 % of all eligible patients are referred to a PC physician. Rather, it is essential to evaluate what circumstances make it possible (or not) to implement EPC. For this reason, the qualitative arm of this study will assess the strengths and weaknesses of this model of EPC along with potential areas of improvement from the perspective of all stakeholders (PC physicians, oncologists/department heads, patients and caregivers).

### Qualitative data collection in the preliminary and main study phase

The responsible research assistants from the Department of Palliative Care in Freiburg will work in close cooperation with the PC physician at each CCC to coordinate logistics and dates for the interviews in each of the four interview studies. The interviews will be conducted by interviewers who have received a training in qualitative interview methods.

### Qualitative data analysis

The guided interviews will be analyzed after transcription using the principles of qualitative content analysis. A team of researchers will inductively develop a category system in order to create a subject matrix for each of the four interview studies [21]. Content analysis will be aided by the use of the software program MAXQDA.

### Ethics

The study has been designed according to the Declaration of Helsinki [22]. The study protocol was approved by the Ethics Committee of the University of Freiburg, Germany (vote: 193/14, date: 25 April 2014) and the responsible data protection officer. In addition, ethical approval was obtained from the Ethics Committee of the University of Tuebingen, the Ethics Committee of the Mannheim University Hospital, the Ethics Committee of the University Medical Center Heidelberg, and the Ethics Committee of the University of Ulm. Consistent with good clinical practice, patients will be informed about participation in the study, its implications and written consent will be obtained.

## Discussion

The primary objectives of the implementation of EPC in our study are (1) to identify patients with unmet palliative care needs, (2) to advise patients regarding the possibilities of specialized PC in their particular situation, (3) to reduce inhibitions to make use of palliative care as a normal part of the center’s treatment options, (4) to create a “double awareness” for the will to survive (“fight against cancer”) and inevitable mortality, and (5) to prevent that PC is misunderstood as only end-of-life care.

Concerns have repeatedly been raised that cancer treatment will become disintegrated if treatment is too interdisciplinary [23]. Therefore, EPC must occur in close cooperation and communication with all other responsible departments (e.g. the oncology department). Above all, it is important that the patient maintains a feeling of security and does not become confused by conflicting messages regarding prognosis and treatment goals. Patients and their family/caregivers must always be aware who is primarily responsible for their care (typically this will be a physician from the oncology, radiation therapy or senology department) [11]. The model of EPC implemented in this study takes this premise very seriously. Based on clinical and administrational experiences from our EPC pilot study [7], we are convinced that EPC can only be successfully integrated into standard oncology care when there is close cooperation between PC and cancer specialists [24]. This goal also serves to establish clear areas of responsibility for everyone involved. Accordingly, the PC physician advises the patient, his family and the primary treating physician but refrains from becoming involved in decision-making regarding disease-modifying therapies. The most basic principle of this approach is to avoid conflicting messages and establish a trustful relationship between the patient and the primary physician.

The main goal of the study proposed here is to test the feasibility of implementing a routine EPC program into the standard oncology care of CCCs. In addition, we are interested in 1) describing the type of support that patients would like from palliative care, (2) gaining information about the effect of palliative care on patients’ QoL and healthcare costs, and (3) determining which factors could potentially ease or hinder the implementation of EPC, respectively. The long-term goal of this project is to create sustainable improvements in the care of patients with incurable, life-limiting cancer.

From the perspective of health services research, so-called “real-world” studies are urgently needed to gather accurate information about the effects of complex interventions (e.g. implementation of EPC) outside of artificial study conditions [25]. To our knowledge, no (inter‐)national study until now has investigated the feasibility – in the sense of “putting evidence into practice” – of the routine integration of EPC into everyday clinical practice at CCCs.

Synergistic, relevant effects from this project have the potential to lead to sustainable improvements in the care of patients with life-limiting illnesses. Thus, this project should serve as a catalyzer. Local palliative care teams should be put in position to routinely cooperate with the primary treating department at their respective cancer center. In addition, this project aims at publicly raising awareness for the need of supportive palliative care, aimed at accompanying patients throughout their care and reducing unnecessary suffering. Further, valuable information regarding the design of future studies and improvements in patient care can be gained from this study.

## Abbreviations

PC: Palliative Care EPC Early Palliative Care
NSCLC: Non-Small Cell Lung Cancer
QoL: Quality of life
ASCO: American Society of Medical Oncology
CCC: Comprehensive Cancer Center
POS: Palliative Outcome Scale
EORTC: European Organization for Research and Treatment of Cancer
HADS: Hospital Anxiety and Depression Scale
